### Data Collection

Firstly, self-reported responses are collected by use of Internet-based survey, accessed online, or sent to participants via email (Table 2). Surveys will be hosted by “KeySurvey”, an in-house survey infrastructure available at UNSW [33]. All completed responses will be stored securely in a server managed by UNSW. These surveys are:

Secondly, during the study, participants’ actions on the *Healthy.me* system will be unobtrusively and automatically logged.

Thirdly, a subset of participants (up to 10% of the sample) may be selected, according to their experiences and their patterns of behaviors using *Healthy.me*, for a post-study semi-structured interview/focus group, eliciting their feedback on *Healthy.me* and asthma self-management.

### Analysis Plan

Statistical significance is defined as a *P*-value of less than .05 (determined using a two-tailed test). Data will be collected by online survey software KeySurvey [33] and analyzed using IBM SPSS Statistics 19 [34].

#### Baseline Comparison

Comparisons of baseline variables between PCHMS group and control group will be conducted using visual inspection, to verify the absence of abnormal measures and data. An assessment of the homogeneity of the variances of distributions from the two groups will be statistically verified before carrying out inferential statistical analyses.

#### Primary Analysis

Differences in proportions of participants visiting their GP to obtain/update their written asthma action plan during the study will be compared between control and PCHMS groups. All intervention recipients who had the opportunity to use the PCHMS but did not do so will be included in the primary analysis (intention-to-treat principle with Last Observation Carried Forward (LOCF) imputation procedure for missing values [35,36]). Differences in participant proportions between control and PCHMS groups will be analyzed using χ^2^test or Student’s *t*-test. Proportions will be reported with 95% confidence intervals. Adjustments for baseline characteristics and possible confounders, such as age and other demographics [2,3], smoking status [3], and asthma severity [2], will be made through the use of sequential logistic regression [37]. All baseline characteristics, and factors that may affect the written asthma action plan possession rate collected at post study (eg, past possession of an asthma action plan) will be entered at step 1 of the regression; and group allocation (PCHMS vs. control) will be entered at step 2.

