### Sample Size

A conservative estimate of at least 300 participants with 150 in each arm is needed to detect a 15% point difference in possession rate of a written asthma action plan between the control group (14.4%) and the intervention group (29.4%). This estimate is calculated at 5% level of significance, 80% power (2-sided test), with an anticipated participant dropout rate approximately 25%.

The effect size estimate is based on previous studies using *Healthy.me* assessing the efficacy of Internet-based interventions on the uptake of preventative health actions [23], and on studies with interventions promoting the use of personal asthma action plans [13]. The base rate is the percentage of adults (ie, 15 years and over) with current asthma in Australia and possessing a written asthma action plan, reported in the Australia Centre for Asthma Monitoring analysis of the Australian Bureau of Statistics National Health Survey 2007-2008, and cited in the Australia Centre for Asthma Monitoring 2011 report [2].

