**Primary outcome**					
	Number of participants with a written asthma action plan	Pre and post-study surveys	X		X

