## Discussion

### Limitations

There are several potential limitations in this study. Firstly, the number of participants meeting inclusion criteria at study completion might be low because the study will focus recruitment only in Australia. The other inclusion criteria such as age, Internet access, and English speaking skills, might be also restrictive for recruiting participant in the targeted population.

Secondly, there is a possible high attrition rates*.* The study’s outcomes will rely on data from participants’ self-reports. Due to the long duration of the study, over 12 months, it is possible to observe a high rate of attrition from participants and thus, a significant loss of data. To limit this, all participants will be actively requested to complete questionnaires by receiving monthly reminders via emails. Furthermore, the questionnaires used on a monthly-basis will be easy and convenient complete (short questionnaires with an online completion using multiple-choice questions).

Thirdly, there may not be representative of consumers with asthma. The study may be more appealing to younger participants who are interested or literate in computers, the Internet, or asthma self-management topics. These participants may be more enthusiastic about health and the Internet than the general asthma population.

Fourthly, as this is a pragmatic trial of a multifaceted intervention in a complex environment, it is possible that baseline variables associated with participants might also influence the outcome. For example, having a prior history of obtaining a written asthma action plan may predict future planned visits to GP, independent of any additional intervention. We will identify potential baseline variables that might influence outcomes, including age and smoking status, and test for unequal variance in the distribution of these variables in the intervention and control populations.

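### The primary analysis carries the last observation forward, but the only earlier observation of the primary outcome predates allocation, so imputed values say nothing about what happened during the study

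*Protocol article*

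**What the plan says.** All references are to the protocol article.

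- **Outcome.** Outcome Measures and Primary Analysis both define the primary outcome as an event in follow-up: a plan obtained, or an existing plan updated, with a GP during the study. Table 1 labels it more loosely, as having a plan.
- **Timing.** Table 1 gives the source as "Pre and post-study surveys" and marks Baseline and Completion, not Monthly. Table 2 describes the monthly questions as covering symptoms, effect on work and study, and competing demands; the action plan is not among them.
- **Allocation.** Under Allocation Concealment and Assessment, participants learn their group only after completing the pre-study questionnaire.
- **Missing data.** Primary Analysis prescribes an "intention-to-treat principle with Last Observation Carried Forward (LOCF) imputation procedure for missing values".
- **Expected loss.** Sample Size has an "anticipated participant dropout rate approximately 25" per cent. Limitations adds that "it is possible to observe a high rate of attrition from participants and thus, a significant loss of data".

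**The concern.** LOCF needs an earlier measurement of the same quantity, taken after treatment began, to have any claim to be informative. Here there is none. For anyone who does not return the post-study survey, the last observation is the pre-study answer. That answer can record that a person already has a plan; it cannot record that a plan was obtained or updated in the following year. About a quarter of the primary data set could be filled in this way.

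Two consequences follow. The imputed participants contribute no contrast between the arms, so the estimate is pulled toward zero unless dropouts truly gain nothing. If dropout differs by arm, the arms receive different amounts of baseline status, and a difference can appear where none exists.

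**Working it through.** **Inputs from Sample Size.** Control rate 14.4%, intervention rate 29.4%, two-sided 5%, 80% power, 150 per arm, about 25% dropout. No dropout figure per arm is given.

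**Assumed inputs.** The trial's own baseline possession rate, b, is not given. I use the 14.4% planning rate and vary b from 0% to 40%, taking b as the same among dropouts in both arms. Dropout splits of 20%/30% and 15%/35%, in either direction, are also assumptions; both average the planned 25%.

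**1. The plan's own figure.** With pooled variance and no continuity correction, the mean rate is 0.219 and

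n = [1.96·√(2 × 0.219 × 0.781) + 0.8416·√(0.144 × 0.856 + 0.294 × 0.706)]² / 0.15² = 118.1, so 119 per arm.

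119 × 1.25 = 149 per arm, or 298 in total, which reproduces the stated 300. (Dividing by 0.75 would give 159 per arm.)

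**2. Power with completers only.** 150 × 0.75 = 112.5 per arm. Power = Φ[(Δ − 1.96·SE0)/SE1], where SE0 uses the pooled rate and SE1 the separate rates. SE0 = 0.0551 and SE1 = 0.0542, so Φ[(0.150 − 0.1081)/0.0542] = Φ(0.773) = 78.0%. The sample size thus fits an analysis of completers, and this is the fair comparator for LOCF.

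**3. LOCF with equal dropout.** Rate in each arm = (1 − d) × during-study rate + d × b. With d = 0.25, and dropouts assumed to have had the same during-study rates as completers:

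- Difference = 0.75 × 15 = 11.25 points, whatever b is.
- b = 14.4%: control 14.4%, intervention 0.75 × 29.4 + 0.25 × 14.4 = 25.65%. With 150 per arm, SE0 = 0.0462 and SE1 = 0.0458, so power = Φ[(0.1125 − 0.0906)/0.0458] = Φ(0.479) = 68%.

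| Carried-forward rate b | Control | Intervention | Power, 150 per arm |
|---|---|---|---|
| 0% (all dropouts counted as no) | 10.8% | 22.05% | 75% |
| 14.4% | 14.4% | 25.65% | 68% |
| 40% | 20.8% | 32.05% | 60% |

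At b = 14.4%, 80% power would need 198 per arm.

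**4. LOCF with unequal dropout and no true effect.** With event rate p in both arms,

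spurious difference = (d_int − d_ctrl) × (b − p).

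The table takes dropout as higher in the intervention arm. Reversing the split reverses the sign and leaves the rejection rate unchanged.

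| p | b | Dropout control/intervention | Spurious difference (points) | Rejection at nominal 5% |
|---|---|---|---|---|
| 14.4% | 14.4% | any | 0 | 5% |
| 29.4% | 14.4% | 20%/30% | −1.5 | 6% |
| 29.4% | 14.4% | 15%/35% | −3.0 | 9% |
| 14.4% | 40% | 20%/30% | +2.6 | 8% |
| 14.4% | 40% | 15%/35% | +5.1 | 19% |
| 29.4% | 0% | 20%/30% | −2.9 | 9% |
| 29.4% | 0% | 15%/35% | −5.9 | 23% |

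Across this grid the nominal 5% test rejects between 5% and 23% of the time.

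**The case against.** Several counter-arguments have force.

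- **The dilution may be real.** People who stop answering surveys may also stop using the site. If dropouts in the intervention arm gain nothing, a smaller effect is closer to the truth. This stands, and makes the 11.25 points conditional. It supports an explicit missing-as-not-obtained analysis, not one that counts prior holders as successes.
- **Possession may be the intended outcome.** Table 1 and Sample Size speak of having a plan, and baseline possession is then an earlier value of the same variable. Even so, a value taken before allocation holds no information about the intervention.
- **Differential dropout is not established.** A static page might lose more controls, but the Control section promises them the full system after 12 months, and both arms receive the same survey emails and reminders. No direction can be presumed.
- **Inflated type I error is not shown.** A reader might infer that LOCF will produce false positives, perhaps at around 20%. The document does not support that: such figures need a large assumed dropout gap together with a baseline rate far from the event rate. With both at the document's own 14.4%, the bias is exactly zero.
- **Standard errors.** A reader might also say that treating imputed values as observed makes the standard error wrong. That is a fair general caution about single imputation, but it has not been quantified here and the point does not rest on it.

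**Conclusion.** The point holds. LOCF is a stated rule for the primary analysis, not a detail left to an analysis plan, and the only value it can carry forward predates allocation. That defect needs no assumption about rates.

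The size does. With equal 25% dropout, and dropouts who would have had completers' rates, LOCF costs a quarter of the design difference. It leaves about 68% power (60% to 75% over the assumed baseline range), roughly 10 points below the 78% available from completers; the further 2 points to the stated 80% are not due to LOCF. With unequal dropout, the bias may be zero, positive or negative, depending on quantities that the document does not give. Because the rule governs the primary result, it should be changed before allocation is unblinded.

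**What to change.** Delete LOCF from Primary Analysis. Analyse all randomised participants with multiple imputation of the month-12 outcome, done separately by arm, using gender, asthma severity, baseline plan possession, age, smoking and whatever monthly control and exacerbation responses are available. State that this assumes data are missing at random given those variables.

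Add two sensitivity analyses: missing counted as not obtained or updated in both arms, and a delta-adjusted tipping-point analysis. The first has its own bias under unequal dropout (the b = 0% rows above), so it should not stand alone; its merit is that the assumption is explicit.

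The cost is revised wording, modest programming and a wider, more honest confidence interval. No new data are needed. Monthly responses may be sparse for the very people who drop out, so imputation may recover little; that is why the sensitivity analyses are needed.

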**Methods:**

The PCHMS integrates an untethered personal health record with consumer care pathways and social forums. After eligibility assessment, a sample of 300 adult patients with moderate persistent asthma will be randomly assigned to one of these arms. After 12 months of using either Healthy.me or information websites (usual care arm), a post-study assessment will be conducted.

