### Participants

Participants meeting eligibility criteria will be invited to use *Healthy.me* for 12 months. Participants will be assigned to intervention (access to *Healthy.me*) or control (access to static website) by random allocation generated by a computerized random-number generator [28]. Participants may be randomly selected to attend a 1-hour interview (or focus group) to discuss their asthma management and feedback at the end of the study. The participant inclusion eligibility criteria are as follows: (1) aged 18 or above, (2) living in Australia at the time of the study, (3) easy access to the Internet and email on a regular basis, (4) doctor diagnosis of asthma, and (5) adequate English reading and written ability. Participants currently enrolled in other trials of *Healthy.me* are excluded.

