#### Randomization

After consent each participant is randomly allocated to the intervention or control group, stratified by gender and level of asthma severity (intermittent vs. persistent), according to a sequence generated by a computerized random-number generator [28] using permutated blocks of 2, 4, and 8. The randomization sequence generation, participant enrolment and group allocation processes in this study are computerized online and do not involve interference from the investigators.

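### The primary test ignores the stratified randomisation, the adjusted model beside it is not named as confirmatory, and the study population is stated inconsistently

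*Protocol article*

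**What the plan says.** **Randomisation.** Allocation is by permuted blocks, "stratified by gender and level of asthma severity (intermittent vs. persistent").

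**Primary Analysis.** The section makes three statements.
- "Differences in participant proportions between control and PCHMS groups will be analyzed using" a chi-square test or a Student's t-test. No strata are mentioned, and there is no rule for choosing between the two tests.
- Adjustment will be made by sequential logistic regression for age and other demographics, smoking status and asthma severity.
- Step 1 of that regression takes all baseline characteristics, together with factors affecting possession that are collected at post study. Past possession of a plan is the example given. Group enters at step 2.

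**Limitations.** The protocol expects that "having a prior history of obtaining a written asthma action plan may predict future planned visits to GP". Table 1 shows plan possession surveyed at baseline and at completion.

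**Population.** The Abstract says that "a sample of 300 adult patients with moderate persistent asthma will be randomly assigned to one of these arms". The Participants section asks only for a "doctor diagnosis of asthma" and sets no severity limit. The Randomization section has an intermittent stratum.

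**The concern.** Blocking within strata makes the arms more alike on gender and severity than an unstratified test assumes. If those factors predict the outcome, the unstratified standard error is somewhat too large and some power is lost. Pre-study plan possession, which the protocol itself singles out as a likely predictor, plays no part in the first-named test.

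The adjusted regression could repair both, but the text does not make it the confirmatory result. Whether the trial's conclusion rests on the unadjusted or the adjusted P value is therefore open. The regression also appears to draw a key covariate from the post-study survey. A report of past possession given after 12 months of open-label exposure can be affected by the arm, which a pre-study report cannot.

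The population matters for two reasons: it fixes whom the conclusion covers, and it decides whether the severity stratum has one level or two.

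**Working it through.** **1. The plan's own figure.** Inputs from Sample Size: 14.4% vs 29.4%, two-sided 5%, 80% power, 25% dropout, 150 per arm. With pooled variance and mean rate 0.219:

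n = [1.96·√(2·0.219·0.781) + 0.842·√(0.144·0.856 + 0.294·0.706)]² / 0.15² ≈ 118.1, so 119 evaluable per arm.

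119 × 1.25 gives 149 per arm (298 in total), which reproduces 300. Dividing instead by 0.75 gives 159 per arm (318). With 25% loss, 150 × 0.75 = 112.5 are evaluable per arm, and the power of the unstratified test is 78.0%. The checks below use 112 per arm.

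**2. What the strata alone are worth.** The documents give no outcome rates by gender or severity, so the odds ratios (OR) are assumptions. Simulation with four equal strata, balanced arms, overall rates held at 14.4% and 29.4%, and 100,000 runs per row:

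| Gender OR | Severity OR | Chi-square | Cochran-Mantel-Haenszel |
|---|---|---|---|
| 1 | 1 | 78.3% | 78.4% |
| 1.5 | 2 | 78.6% | 79.4% |
| 1.5 | 3 | 78.8% | 80.5% |
| 2 | 4 | 79.4% | 81.9% |
| 2 | 6 | 79.7% | 83.3% |

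The mechanism is the ratio of within-stratum to overall variance. For gender 1.5 and severity 2, the average within-stratum variance is 0.1209 (control) + 0.2010 (intervention) = 0.3219. The overall value is 0.144·0.856 + 0.294·0.706 = 0.3308. The ratio is 0.973. In the last row it is 0.871. If only gender is prognostic (OR 1.5 to 2), the gain is under 1 point.

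**3. What pre-study possession adds.** Logistic regression, 112 per arm, gender not prognostic, severity OR 2.7, possession OR 6, 30% holding a plan at baseline (all assumed), event rates 17.3% vs 32.4%, 6,000 runs:
- chi-square: 76.4%
- logistic with strata only: 77.3% (+0.9)
- logistic with strata and pre-study possession: 82.3% (+5.0 more)

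At the protocol's own 14.4% vs 29.4%, again with 6,000 runs per row:

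| Severity OR | Possession OR | Holders at baseline | Chi-square | Strata and possession |
|---|---|---|---|---|
| 2.7 | 6 | 30% | 78% | 84% |
| 2.7 | 6 | 14.4% | 78% | 83% |
| 2 | 3 | 30% | 79% | 81% |
| 1 | 1 | – | 79% | 78% |

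The Monte Carlo standard error is about √(0.78·0.22/6000) = 0.5 points, so the last row shows no difference.

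**4. Validity of the unstratified test.** Null rejection of the chi-square was 4.0% to 5.2% across the strata scenarios, with the lowest value at gender OR 2 and severity OR 6. The t-test gave 3.8% to 4.9%. The powers of the two tests agreed within 0.01 points.

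**5. Population, side by side.** Abstract: moderate persistent only. Participants: any doctor-diagnosed asthma. Randomization: intermittent and persistent. The second and third are compatible; neither fits the first. If the Abstract is right, the severity stratum has one level and contributes nothing to step 2.

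**The case against.** The strongest reply is that the plan already contains the adjusted model. The regression stands under the Primary Analysis heading, names asthma severity and past possession, and covers gender through demographics and the entry of all baseline characteristics. The proposed model is close to a subset of it. That stands: a reader might infer that the plan ignores its stratification factors, and the text does not support this. What remains is narrower. The confirmatory result is not identified, gender is not named, and past possession is described as a post-study item. An unseen analysis plan may settle the first, but the article sets out the tests itself and leaves them competing.

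Three further inferences are tempting and do not hold.
- *That the unstratified test throws away about 6 points of power because of the strata.* At a severity odds ratio of 2.7 the strata account for about 1 point. The rest depends on an assumed odds ratio of 6 for possession, which is not a stratification factor.
- *That the primary P value is materially conservative.* Null rejection stays near 5% unless the strata are very strongly prognostic. Using an unstratified test after stratified randomisation costs some efficiency and is not an error.
- *That offering a t-test gives a real second chance at significance.* For a binary outcome at this size it is practically the same test. The phrase is loose drafting.

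On population, a reader might take the Abstract to be the slip because two Methods sections disagree with it. The documents do not settle which passage is to be corrected.

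**Conclusion.** The point holds in a limited form. The named primary test does not reflect the stratified design, and the choice between unadjusted and adjusted results is open. Past possession should come from the pre-study survey. The chi-square test is valid.

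The gain from a primary model with the strata and pre-study possession is about 0 to 6 points of power at 112 evaluable per arm, for assumed odds ratios of 1 to 2.7 (severity) and 1 to 6 (possession). The strata's share is about 0 to 1 point at those values, and up to about 3.6 points at gender OR 2 and severity OR 6. None of these odds ratios, nor the 30% share of baseline holders, is in the documents.

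The contradiction over the study population rests on no assumption and stands as stated.

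**What to change.** - Name one primary analysis: logistic regression of plan obtained or updated (yes/no) on arm, gender, severity and pre-study plan possession. Report a standardised risk difference with its 95% confidence interval.
- Use only covariate values recorded before allocation. The Allocation Concealment section says the arm is revealed after the pre-study questionnaire, so the possession value in Table 1 is suitable. Keep post-study items out of this model.
- Keep the plain chi-square as a supportive analysis and delete the t-test alternative.
- Reconcile the Abstract, Participants and Randomization sections on asthma severity. If only persistent asthma is intended, the severity stratum and the severity term in the model need revisiting.

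The analysis changes need wording only, with no extra data or participants. The population change is also wording if the broader eligibility was intended. If the narrower population was intended, eligibility and stratification would have to be revised, and recruitment is described as ongoing.

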## Methods

### Study Design

A randomized controlled trial with a 2-group parallel design (with intervention allocation ratio 1:1) will be used to evaluate the efficacy of the Web-based PCHMS *Healthy.me*, reported in accordance to the 2010 CONSORT statements [27](ACTRN12612000716864). The PCHMS is not part of usual care but aims to improve usual care as measured by compliance to evidence-based guidelines.

Participants randomized to the *intervention* group will have immediate access to an interactive version of *Healthy.me* with full PCHMS features as described later, from the date they are recruited.Participants randomized to the *control* group will receive access to a static webpage, without PCHMS features or any interactive component. This webpage will offer links to Australian information websites about asthma.

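### The adjusted primary model has no limit on its covariates, while the expected 49 to 66 events support only about 5 or 6 parameters

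*Protocol article*

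**What the plan says.** The Primary Analysis section first compares the arms by a chi-square test (or t-test) on proportions, by intention to treat with last observation carried forward. It then adds a sequential logistic regression and names age, other demographics, smoking status and asthma severity as examples of what to adjust for. The rule for step 1 is wider than those examples: "All baseline characteristics, and factors that may affect the written asthma action plan possession rate" all go in, and group allocation follows at step 2. No number of variables, selection rule or penalisation is given.

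The Sample Size section says "A conservative estimate of at least 300 participants with 150 in each arm is needed", for a plan-possession rate of 14.4% against 29.4% with about 25% dropout. That calculation is for the unadjusted difference. The Limitations section adds: "We will identify potential baseline variables that might influence outcomes, including age and smoking status", and goes on to say that the distributions of these variables will be compared between arms.

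**The concern.** Ordinary maximum-likelihood logistic regression needs enough events for the number of parameters it estimates. When events per parameter are few, a real effect is estimated too far from 1, and tests of a single term can reject slightly too often. The pre-study survey takes 10 minutes and covers demographics and experience of asthma management (Intervention and Control section; Table 2). A model that takes in every baseline characteristic, with categories expanded to indicators, could therefore have many terms. The adjusted odds ratio sits under the primary analysis heading and would probably be reported beside the chi-square result, so an inflated value would be visible. This is a rule that the article states, not a detail left to a later document: a short list in an analysis plan would depart from it.

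**Working it through.** **Inputs** (Sample Size and Study Design sections): control 14.4%, intervention 29.4%, two-sided 5%, 80% power, dropout about 25%, 150 per arm, 1:1.

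**The plan's own figure.** Pooled two-proportion formula, mean rate 0.219:

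n = [1.960·√(2×0.219×0.781) + 0.842·√(0.144×0.856 + 0.294×0.706)]² / 0.15² ≈ 118.1, so 119 per arm.

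119 × 1.25 ≈ 149 per arm (298 in total), which reproduces the 300 when dropout is added as a 25% mark-up. Dividing by 0.75 would give 159 per arm, but nothing below depends on that.

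**Expected events.**
- Completers: 150 × 0.75 = 112.5 per arm; 112.5 × (0.144 + 0.294) = 16.2 + 33.1 = 49.3. The total is the same if all 300 are analysed and every dropout counts as having no plan.
- Carried forward: Table 1 measures the primary outcome only at baseline and completion, so the one earlier value for a dropout is baseline possession. If that is 14.4% (assumed), the 75 dropouts add 75 × 0.144 = 10.8, giving 60.1.
- All 300 at the planning rates: 150 × 0.438 = 65.7.

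**Parameters supported at 10 events each:** 49.3/10 = 4.9 to 65.7/10 = 6.6, so about 5 or 6 including the arm.

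**Simulation.** Independent, non-prognostic covariates; true odds ratio (0.294/0.706)/(0.144/0.856) = 2.48; type I error evaluated with 21.9% in both arms. Because the covariates are unrelated to outcome, non-collapsibility cannot explain a drift. Each cell shows 224 participants / 300 participants; events per parameter use 49.3 / 65.7 events and count the arm.

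| Covariates | Events per parameter | Median adjusted OR | Ratio to 2.48 | Likelihood-ratio type I error |
|---|---|---|---|---|
| 5 | 8.2 / 11.0 | 2.53 / 2.56 | 1.02 / 1.03 | 5.6% / 6.5% |
| 10 | 4.5 / 6.0 | 2.63 / 2.57 | 1.06 / 1.04 | 5.4% / 5.3% |
| 20 | 2.3 / 3.1 | 2.79 / 2.68 | 1.13 / 1.08 | 6.7% / 5.4% |
| 30 | 1.6 / 2.1 | 2.95 / 2.83 | 1.19 / 1.14 | 7.8% / 6.4% |

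Cells used 1,500 to 5,000 trials, so the Monte Carlo standard error at 5% is about 0.6 to 0.3 points. In the 5-covariate run at 300, the chi-square test itself rejected in 5.8%, so most of the 6.5% is noise. Under no effect the median odds ratio stays at about 1.0.

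A second run (2,000 trials per cell, half the covariates binary at 20%) gave, for 10, 20 and 30 covariates:
- 112 per arm: average OR 2.62, 2.81, 3.05; likelihood-ratio type I error 6.4%, 6.2%, 8.5%.
- 150 per arm: average OR 2.60, 2.69, 2.83; likelihood-ratio type I error 6.5%, 6.8%, 8.5%.

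**Power** at 224 participants, adjusted Wald test against chi-square: 77.2% v 78.0%, 77.2% v 78.7% and 76.0% v 78.2% for 10, 20 and 30 covariates. It does not rise.

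**A less favourable case.** With five mildly prognostic covariates among those entered (true conditional OR 2.73, 112 per arm), 10, 20 and 30 covariates gave 3.02, 3.20 and 3.57, which are ratios of 1.11, 1.17 and 1.31. So 20% is not a ceiling when the list is very long.

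**The case against.** The strongest reply is that this does not touch the main result. The sample size and the first-named test concern the unadjusted proportions, and the regression supports them. That is correct and limits the reach of the point.

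Second, the article never counts its covariates. The word *all* could refer back to the few examples in the preceding sentence, and an itemised list is something an article may leave to the full protocol. This also stands in part: overfitting is a risk that depends on the length of the list, not an established fact. But the wording as printed is unrestricted and adds further factors, so it does not hold the model to a short list.

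Third, 49 is a completer count, whereas the stated analysis keeps all randomised participants. Hence the range of 49 to 66. The upper end still supports only about 6 parameters.

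Two stronger readings are tempting. A reader might infer that the adjusted analysis exaggerates significance as much as it exaggerates the odds ratio. The calculations do not support this: power is slightly lower than for chi-square, and the excess type I error is a few points at most. A reader might also take the Limitations passage as a rival, data-driven rule for choosing covariates. Read to its end, that sentence describes a comparison of baseline distributions between arms, in line with the Baseline Comparison section. It does not mention the regression, so it is not a contradiction.

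**Conclusion.** The point holds as a caution about the adjusted analysis. The step 1 rule is open-ended, and the planning figures supply about 49 to 66 events. With 10 to 30 covariates the odds ratio is exaggerated by about 5 to 20%. The likelihood-ratio type I error for the arm is about 6 to 9%: individual cells with non-prognostic covariates ran from 5.3% to 8.5%, highest at 30 covariates. With about 5 covariates the effect is negligible.

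This rests on three assumptions: the number of covariates, which the article does not give; independent covariates without rare categories, since sparse categories could do worse; and event rates borrowed from plan possession, although the outcome is a plan obtained or updated during the study. The documents do not support saying that the model is certainly overfitted or that the trial's main test is compromised.

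**What to change.** In the Primary Analysis section, replace the open-ended step 1 wording with a short, prespecified list of variables measured before randomisation. An example is the two stratification factors in the Randomization section (gender and asthma severity), plan possession at the pre-study survey, age and smoking status. At one parameter each, plus the arm, that makes 6 parameters: 49.3/6 = 8.2 to 65.7/6 = 11.0 events per parameter, the range in which the simulations show little distortion. If a longer list is kept, fit it by Firth-penalised logistic regression.

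The cost is a change of wording, with no new data; minor covariates are left out. The Limitations text can stay, because it describes a check of baseline balance.
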